#### Parents’ measures

##### Parental affection, behavioural control, and psychological control

Parents’ or legal guardians’ perceptions of their provision of affection-, behavioural control-, and psychological control towards their child will be measured using three scales [29]: the seven-item parental affection scale (e.g., “I respect my child’s opinions”), the six-item parental behavioural control scale (e.g., “When I am angry at my child, I let him/her know about it”), and the four-item parental psychological control scale (e.g., “My child should be aware of how much I sacrifice for him/her”). Responses will be provided on five-point scales (1 = *not like me at all* and 5 = *very much like me*). The scales have exhibited satisfactory psychometric properties in previous research [29].

##### Parental provision of autonomy support towards out-of-school physical activity

Parents’ or legal guardians’ perception of their provision of autonomy support towards out-of-school physical activity will be measured using a four-item scale (e.g., “I encourage my child to be physically active in free-time”) based on the PASSES [44]. Responses will be provided on 7-point scales (1 = *strongly disagree* and 7 = *strongly agree*).

#### Demographic variables

We will also ask participating PE teachers to self-report the following demographic details: age, gender, education, years of teaching experience, and number of students in their PE class. In addition, we will collect self-reported demographic details from participating students: age, grade, gender, and school. We will also collect the following demographic details from participating parents: gender, nationality of a child, ethnicity of a child, and highest level of education. A summary of study measures, data collection occasions and methods is provided in Additional file 1.

### Sample size

A statistical power analysis was conducted to estimate the required sample size for student data based on a path analysis according to published recommendations [56]. The analysis was based on a model in which the primary outcome variable of student’s participation at each post-intervention follow-up occasion was regressed on the intervention condition (dummy coded as 1 = received intervention, 0 = received control) and constructs from the trans-contextual model (perceived autonomy support, autonomous motivation in PE and out-of-school, attitudes, subjective norms, perceived behavioural control, and intentions) as simultaneous predictors. Statistical power (beta) was set at 0.90 and statistical significance level (alpha) was set at 0.05, and confidence intervals of 0.068 and 0.080 for the root mean square error of approximation fit index based on previous trans-contextual models [9]. The analysis indicated that a student sample size of 286 is required to detect the effect size based on model fit. Based on typical attrition rates of 40% reported in the literature in multiple follow-up studies of physical activity [57, 58] we aim to recruit 476 student participants at baseline (*n* = 238 participants per intervention group).

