##### Autonomous motivation, controlled motivation and amotivation toward in school and out-of-school physical activity

Autonomous and controlled forms of motivation for in-school and out-of-school activities will be measured using a modified version of the perceived locus of causality questionnaire [46], and amotivation using modified version of amotivation subscale from the sport motivation scale [47]. The total scale consists of ten items with two items measuring each of the external regulation (e.g., “I do PE/ physical activity so that the teacher won’t yell at me”), introjected regulation (e.g., “I do PE/physical activity because I would feel bad if the teacher thought that I was not good at PE”), identified regulation (e.g., “I do PE/physical activity because it is important to me to do well in PE/physical activity”), intrinsic regulation (e.g., “I do PE/physical activity because it is fun”) and amotivation (e.g., I do PE/ physical activity but I ask myself why I do it) constructs. Responses will be provided on 7-point scales (1 = *not true for me* and 7 = very true for me). For each of the PE and out-of-school contexts, autonomous motivation scores will be computed as an average of scores on the identified regulation and intrinsic regulation items, and controlled motivation scores will be computed as an average of scores on the external regulation and introjected regulation items. Amotivation will be measured with responses provided on the same seven-point scales. Measures for autonomous and controlled motivation have demonstrated satisfactory construct validity and internal consistency statistics in previous studies [45] and measure for amotivation has demonstrated adequate level of internal consistency [47].

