### Data analysis

Multilevel structural equation modelling using the Mplus, v. 8.0 software [59] will be used to test our hypotheses. All analyses will be performed using intention-to-treat analysis and supplemented by per-protocol analyses for all planned outcome variables [60]. Where data is missing for the psychological variables, we will impute missing values using linear interpolation if the data is confirmed missing completely at random. We expect to have data on our primary and secondary outcome measures, as well as mediating measures, at pre-trial and at the allotted follow-up occasions after the delivery of the intervention (post-trial, and at the one-, three-, and six-month follow up data collection occasions after the implementation period). We also expect to have self-report data on parenting from students and their parents or guardians at pre-trial. Student data will be nested within school and teacher/class, and therefore variance in outcome variables may be attributable to school-level and class-level variation as well as variation between students attributable to the intervention itself. Effects of the intervention on study outcomes can be interpreted at the student level after controlling for school- and class-level effects. Our longitudinal design enables also the examination of potential trajectories in the development of outcome variables. We will test the model at each of the follow-up time points with students’ out-of-school physical activity as the primary dependent variable, the intervention condition as a dummy-coded independent variable (1 = intervention group; 0 = control group), and the psychological variables (perceived autonomy support from teachers, autonomous motivation in PE and out-of-school physical activity, attitudes, subjective norms, perceived behavioural control, intentions), as simultaneous predictors. We will statistically control for each of model variables from the previous time point using the standardized residual scores.

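### The 286 students and 0.90 power cannot come from a fit-index (RMSEA) calculation on the path model described, because that model is saturated

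*Protocol article*

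**What the plan says.** The Sample size section says the calculation was meant to "estimate the required sample size for student data based on a path analysis according to published recommendations". The model has physical activity at each follow-up as outcome. Its predictors are the intervention dummy, perceived autonomy support, autonomous motivation in PE, autonomous motivation out of school, attitudes, subjective norms, perceived behavioural control and intentions, all entered simultaneously. The error rates are given as "Statistical power (beta) was set at 0.90 and statistical significance level (alpha) was set at 0.05". The effect size is expressed through the fit index, with "confidence intervals of 0.068 and 0.080 for the root mean square error of approximation fit index based on previous trans-contextual models". The result is "The analysis indicated that a student sample size of 286 is required to detect the effect size based on model fit". Allowing for 40% attrition, the target becomes 476 students, 238 per group. No degrees of freedom are given, and the text does not say what role each of the two RMSEA values plays.

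Data analysis describes the same model for each follow-up: the condition dummy enters alongside "the psychological variables (perceived autonomy support from teachers, autonomous motivation in PE and out-of-school physical activity, attitudes, subjective norms, perceived behavioural control, intentions), as simultaneous" regressors. The section on mediating variables treats the motivation constructs as observed scores: "autonomous motivation scores will be computed as an average of scores on the identified regulation and intrinsic regulation items".

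**The concern.** A power calculation based on RMSEA tests how well a model reproduces the observed covariances. It is determined by alpha, the RMSEA values, the sample size and the model's df. The article does not print the df, but it describes the model, and that description fixes the df. One outcome regressed on a set of predictors that are free to correlate leaves nothing to test: the model reproduces the covariances exactly, whatever the data. The stated sample size and power would then have no basis in the model they are attached to.

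The 0.90 power and the target of 476 rest on this figure alone, since the section gives no other justification. A reader would take the trial to have 90% power for the analysis described, yet for that analysis the power is undefined even for the fit test it refers to. Whether a fit test is the right basis for sizing a trial of an intervention effect, and whether clustering is allowed for, are separate questions and are not argued here.

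**Working it through.** **1. Inputs.** From Sample size: power 0.90, alpha 0.05, RMSEA 0.068 and 0.080, one outcome, eight predictors (condition plus seven constructs), attrition 40%. Data analysis confirms one model per follow-up occasion.

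**2. Degrees of freedom of the described model.**
- Variables: 1 + 8 = 9.
- Variances and covariances: 9 × 10 / 2 = 45.
- Free parameters: 8 × 9 / 2 = 36 predictor variances and covariances, 8 regression paths and 1 residual variance, in total 45.
- df = 45 − 45 = 0.

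With df = 0 the fit chi-square is identically zero, and RMSEA has no distribution from which to compute power. No sample size follows.

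**3. What reproduces 286 if 0.068 and 0.080 are null and alternative.** The usual method takes the fit statistic as noncentral chi-square with noncentrality (N − 1) × df × RMSEA². The critical value is the one-tailed alpha point under the null RMSEA, and power is the tail probability under the alternative.

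At N = 286 and df = 276:
- noncentrality under 0.068: 285 × 276 × 0.068² = 363.7
- noncentrality under 0.080: 285 × 276 × 0.080² = 503.4
- upper 5% point under the null: 714.9
- power: 0.901

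Reversing null and alternative gives 0.900. The smallest N for 0.90 power at df = 276 is 286 in both directions. Changing alpha moves the required df to about 212 (alpha 0.10) or about 338 (alpha 0.025).

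**4. How large the df could be.** Nine observed scores have 9 × 8 / 2 = 36 covariances, so no path model on them can exceed 36 df. That ceiling is reached only with every path and correlation removed. Results for 0.068 versus 0.080 at alpha 0.05:

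| Model | df | N for 0.90 power | Power at 286 |
|---|---|---|---|
| As described | 0 | undefined | undefined |
| Nine scores, ceiling | 36 | 1,738 | 0.28 |
| All four follow-up outcomes in one model (12 variables), ceiling | 66 | 985 | 0.42 |
| Eight previous-occasion scores added (17 variables), ceiling | 136 | 516 | 0.66 |
| Match to the stated figure | 276 | 286 | 0.90 |
| Item-level latent model (assumed) | 595 | 159 | 0.996 |

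The last row is one assumed latent version. The protocol's item counts give 18 + 4 + 4 + 3 + 2 + 2 + 2 = 35 indicators. Adding condition and activity makes 37 variables and 37 × 38 / 2 = 703 moments. Subtracting 28 loadings, 35 residual variances and 45 structural variances and covariances leaves 595.

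**5. Other readings of the two RMSEA values.** Testing exact fit (null RMSEA 0) at alpha 0.05 and power 0.90:
- against 0.080 at df = 12: N = 286
- against 0.068 at df = 20: N = 284
- against the midpoint (0.068 + 0.080) / 2 = 0.074 at df = 15: N = 289

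Each needs a non-saturated model, which is not what the section describes. The df values of 12, 15 and 20 are assumptions; the article gives none.

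**6. Attrition.** 286 / 0.6 = 476.7, consistent with the stated 476 apart from rounding.

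**The case against.** The strongest defence is that the description is loose rather than the calculation wrong. The text calls 0.068 and 0.080 a confidence interval, not null and alternative values. Read as an interval around RMSEA values seen in earlier models, they give close to 286 for a small chained path model (step 5). Data analysis specifies multilevel structural equation modelling, and the Background describes a mediated chain and a long list of covariates. Simultaneous predictors may therefore be shorthand for a larger model. With 24 observed variables the df ceiling is already 24 × 23 / 2 = 276. A latent model with parcelled items could also land near that value. Finally, a condensed article commonly leaves the df to the full protocol.

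Much of this stands. It rules out saying that 286 arises only at about 276 df, or that no model consistent with the article could give it. It also means that the 0.28 and the roughly 1,740 students are not the power and size of the planned analysis. They require the null/alternative reading and a model with every path deleted, which nobody proposes.

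It does not remove the point. The finding does not depend on a missing df. The article states a model, states it again in Data analysis, and that model has no testable fit. If another model produced 286, Sample size describes the wrong one.

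**Conclusion.** The point holds in a limited form. For the model set out in Sample size and Data analysis, df = 0, so the statement that 286 students give 0.90 power has no meaning. This rests on the literal model description and on one observed score per construct, which the wording on path analysis and on averaged motivation items supports.

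The numerical gap depends on how the RMSEA values are read. As null and alternative at alpha 0.05, they need about 276 df for 286 students, against a maximum of 36 for nine observed scores. As exact-fit alternatives, they give about 286 at 12 to 20 df.

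A reader might infer that 286 is wrong outright, that the trial has only 28% power, or that some 1,740 students are needed. The documents support none of these. They do not state the role of the RMSEA values or the df, and a non-saturated model could have produced 286. What they show is that the stated basis for the sample size and the stated model do not belong together.

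**What to change.** In Sample size, stop attributing 0.90 power to the simultaneous-predictor model. Then do one of two things:
- name the non-saturated model actually used, give its df and say which role 0.068 and 0.080 each play, and bring Data analysis into line with that model; or
- withdraw the 0.90 power.

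In either case keep 476 as the recruitment target (the article expects 502 students to be invited). State the precision or detectable effect that this number gives for the condition coefficient to be reported.

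The cost is one recalculation, a reworded paragraph and possibly a matching sentence in Data analysis. No extra enrolment or change to data collection is needed. The downside is that the stated power is likely to look less favourable.

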### Randomization

The core research team will enroll PE teachers and their students to the trial. Schools (*N* = 11) consenting to participate in the trial will be randomized to the intervention or waitlist control conditions. Randomization will be conducted by a researcher independent of the core research team using a random number generator. After generation of the random allocation sequence, the researcher will seal the names of the schools and their allocation in envelopes. Recruitment of teachers and students for the intervention and wait-list control groups will be drawn from the appropriate clusters. The cluster-randomized design precludes potential for contamination of data across conditions caused by the presence of participants from different conditions within schools. The waitlist-control design ensures that the benefits of a potentially effective intervention are not withheld from control group participants.

### Blinding

The researcher who will conduct the randomization of schools to intervention conditions, and the research assistants who will code the audio-recordings of PE teachers’ lessons at baseline and follow-up time points will be blind to group allocation.

### Data analysis

Multilevel structural equation modelling using the Mplus, v. 8.0 software [59] will be used to test our hypotheses. All analyses will be performed using intention-to-treat analysis and supplemented by per-protocol analyses for all planned outcome variables [60]. Where data is missing for the psychological variables, we will impute missing values using linear interpolation if the data is confirmed missing completely at random. We expect to have data on our primary and secondary outcome measures, as well as mediating measures, at pre-trial and at the allotted follow-up occasions after the delivery of the intervention (post-trial, and at the one-, three-, and six-month follow up data collection occasions after the implementation period). We also expect to have self-report data on parenting from students and their parents or guardians at pre-trial. Student data will be nested within school and teacher/class, and therefore variance in outcome variables may be attributable to school-level and class-level variation as well as variation between students attributable to the intervention itself. Effects of the intervention on study outcomes can be interpreted at the student level after controlling for school- and class-level effects. Our longitudinal design enables also the examination of potential trajectories in the development of outcome variables. We will test the model at each of the follow-up time points with students’ out-of-school physical activity as the primary dependent variable, the intervention condition as a dummy-coded independent variable (1 = intervention group; 0 = control group), and the psychological variables (perceived autonomy support from teachers, autonomous motivation in PE and out-of-school physical activity, attitudes, subjective norms, perceived behavioural control, intentions), as simultaneous predictors. We will statistically control for each of model variables from the previous time point using the standardized residual scores.

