## Abstract

**Background:**

Given the documented decline in levels of physical activity in early adolescence, promoting physical activity in young people is a priority for health promotion. School physical education (PE) is an important existing network in which participation in physical activity beyond school can be promoted to the captive young people. The objective of current article is to present the protocol for a PE teacher-delivered theory-based trial to promote secondary school students’ participation in physical activity out-of-school contexts. The intervention will be guided by the trans-contextual model explaining the processes by which PE teachers’ support for autonomous motivation in the classroom promotes students’ motivation to engage in out-of-school physical activity. We hypothesize that school students receiving the teacher-delivered intervention to promote autonomous motivation toward physical activity will exhibit greater participation in physical activities outside of school, relative to students receiving a control intervention.

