## Background

### Promoting physical activity in school

Epidemiological data consistently indicate that levels of physical activity decline with age [1]. Consistent with these trends, national survey data from Finland indicate a decline in physical activity during adolescent years with only 41% of 11-year olds and 17% of 15-year olds meeting current national guidelines for physical activity [2]. Given that low levels of physical activity are related to increased risk of chronic illness later in life, and increased rates of conditions such as overweight and obesity [3, 4], the promotion of physical activity participation among young people is a public health priority. Physical education (PE) stands in an advantageous position for promoting the benefits of leisure physical activity as it addresses young, diverse and captive audiences [5]. Importantly, it is through PE that young people experience a variety of physical activities, and it is these experiences that may determine future involvement in physical activity during leisure time [6]. One of the primary aims of PE is to provide young people with the necessary motor skills, knowledge and competence to choose and participate in health-related physical activity in their leisure time [7]. Nevertheless, there is relatively little research outlining how PE teachers or PE programs can effectively orient young people toward participation in regular leisure-time physical activity outside of school.

The present article outlines the protocol of a trial in which PE teachers will be trained to support autonomous motivation toward leisure-time physical activity in lower-secondary school students (the PETALS trial). The trial aims to capitalize on school PE as an existing network to promote out-of-school physical activity in secondary school students. The trial will adopt a cluster randomized design and implement an intervention based on psychological theory to train participating teachers in techniques that support school students’ motivation to participate in physical activity in their leisure time outside of school. Trial effectiveness will be evaluated in terms of effects on participating school students’ post-intervention out-of-school physical activity participation. The theoretical basis for the intervention will be described next, followed by the study objectives.

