**Fig. 1 Fig1:**
[figure not shown]
Theoretical framework: Trans-contextual model

The trans-contextual model provides a theoretical framework for developing interventions in educational contexts such as school PE to promote motivation toward, and actual participation in, related activities such as physical activity outside of school. The model implies that strategies aimed at fostering autonomous motivation will promote in-school and out-of-school autonomous motivation toward physical activity, and promote adaptive beliefs and intentions toward out-of-school physical activity and actual physical activity participation. These proposed effects are supported by research demonstrating the trans-contextual effects and confirming the relevant mechanisms involved [10]. The most effective means to support autonomous motivation in school is for teachers to display autonomy-supportive behaviours during PE lessons. Consistent with the model, effects of interventions aimed at promoting autonomy support in students on out-of-school physical activity is expected to be mediated by autonomous motivation in both contexts, beliefs, and intentions. Together, these mediators provide a demonstration of how the intervention functions in promoting physical activity behaviour. In other words, it provides a framework on *how* the intervention works.

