#### Mediating variables

All students will complete a battery of self-report measures of psychological variables based on the trans-contextual model. These factors are expected to reflect the mechanisms by which the intervention affects change in the primary outcome consistent with the model.

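### The only model given for the primary outcome adjusts the intervention term for the hypothesised mediators, so that term is a direct effect; the total effect the trial hypothesises is nowhere named as the effectiveness result

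*Protocol article*

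**What the plan says.** All references are to the protocol article.

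- **Hypothesis** (Abstract, Background): students in the intervention arm "will exhibit greater participation in physical activities outside of school, relative to students receiving a control intervention". This compares the arms as wholes, with nothing held fixed.
- **Effectiveness criterion** (Promoting physical activity in school): "Trial effectiveness will be evaluated in terms of effects on participating school" students' activity outside school after the intervention.
- **Causal route** (Theoretical basis for the intervention, text below Fig. 1): the effect "is expected to be mediated by autonomous motivation in both contexts, beliefs, and intentions". The Mediating variables section says of the psychological measures: "These factors are expected to reflect the mechanisms by which the intervention affects change in the primary outcome consistent with the model".
- **Model** (Data analysis): "We will test the model at each of the follow-up time points". The dependent variable is out-of-school physical activity. The predictors are "the intervention condition as a dummy-coded independent variable (1 = intervention group; 0 = control group), and the psychological variables", seven in all: perceived teacher autonomy support, autonomous motivation in PE, autonomous motivation out of school, attitudes, subjective norms, perceived behavioural control and intentions. Each model variable is also adjusted for its value at the preceding occasion, by standardised residual scores.
- **Power analysis** (Sample size): the same specification, with the dummy and the constructs through "perceived behavioural control, and intentions) as simultaneous predictors".

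**The concern.** The variables placed beside the dummy are the ones the theory says carry the effect. Holding them fixed removes from the dummy's coefficient whatever passes through them. What remains answers a different question: does the intervention change activity by some route other than motivation, beliefs and intentions? The stated hypothesis asks whether it changes activity at all.

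The headline conclusion is at stake. If the dummy coefficient is reported as the effectiveness result, a benefit that works as the theory predicts is understated, and more so the better the theory holds. If the choice between direct and total effect is left until the data are in, the primary result is open to selection. Conditioning on variables measured after randomisation also exposes the coefficient to confounding between mediator and outcome, from which randomisation does not protect it.

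**Working it through.** **1. The plan's own figure.** Sample size asks for 286 evaluable students with 40% attrition: 286 / (1 − 0.40) = 476.67, against the stated 476 (2 × 238). This agrees apart from rounding. The 286 comes from model fit (RMSEA 0.068 and 0.080). The model's degrees of freedom are not stated, so 286 cannot be confirmed. No treatment difference or SD is given, so the sample size does not show which effect is meant to be detected, and no trial-specific size of the problem can be computed.

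**2. What the coefficient estimates.** Let a be the effect of condition on a mediator, b the effect of that mediator on activity, and c′ the effect of condition with the mediator held fixed. In a linear model:

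total = c′ + a·b, so c′ = total − a·b.

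With several mediators, a·b becomes the summed indirect effect. The dummy in the Data analysis model estimates c′; the hypothesis concerns the total.

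**3. Illustration.** All inputs are assumptions: one mediator, total effect 0.30 SD, a = 0.6 SD. For mediated share s, b = 0.30·s / 0.6 and c′ = 0.30 − 0.6·b.

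| Share mediated | b | Indirect a·b | Dummy coefficient c′ | Total |
|---|---|---|---|---|
| 50% | 0.25 | 0.15 | 0.15 | 0.30 |
| 70% | 0.35 | 0.21 | 0.09 | 0.30 |
| 100% | 0.50 | 0.30 | 0.00 | 0.30 |

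Large-sample simulation gave the same coefficients. They depend on the total and the share, not on the choice of a.

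**4. Nominal power, same assumptions.** With 286 / 2 = 143 per arm, a two-sided 5% test and only the tail favouring the intervention counted, power is Φ(δ·√(143/2) − 1.96), where √71.5 = 8.456. For δ = 0.30, 0.15, 0.09 and 0.00 this gives 0.718, 0.245, 0.115 and 0.025. Clustering and the correlation of the dummy with the mediators are ignored, so these show direction only.

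**5. Mediator–outcome confounding.** Assume a common cause of mediator and activity, independent of arm, loading 0.3 on each, with mediator variance within arm of 1. The dummy coefficient shifts by −0.6 × 0.3 × 0.3 = −0.054. The three coefficients become 0.096, 0.036 and −0.054, while the total stays 0.30. The adjusted coefficient is then not a clean direct effect either.

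**6. Adjustment for the preceding occasion.**

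| Model at | Preceding occasion | Status |
|---|---|---|
| Post-trial | Pre-trial | Baseline, harmless |
| One month | Post-trial | Post-randomisation |
| Three months | One month | Post-randomisation |
| Six months | Three months | Post-randomisation |

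Physical activity is itself a model variable. From the one-month follow-up on, the coefficient is therefore also net of whatever effect on activity had already appeared and persisted.

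**The case against.** The strongest reply is that a structural model is being read as a single regression. Data analysis opens with multilevel structural equation modelling, and Sample size and the monitoring section speak of path analysis. The Discussion plans to test intervention effects on the theory-based constructs as secondary outcomes, and to evaluate how the intervention works through them. With those paths in the model, direct, indirect and total effects all come from one fit. In a saturated linear model the total equals the regression without mediators. No sentence says that effectiveness will be judged by the dummy's coefficient. The article is condensed, and the choice of reported parameter is often left to an analysis plan.

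Much of this stands. The right answer can be recovered from the planned data, probably from the planned software run. A reader might infer that the protocol fixes the direct effect as its primary test; it does not, because it names no primary parameter. A reader might also infer that the trial must return about zero, with power at the significance level, even if the intervention works. That needs full mediation and a report confined to the dummy coefficient. The article says the effect is expected to be mediated, not wholly mediated, and Fig. 1 is not available to show whether a direct path is drawn.

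Two things do not fall. First, the difficulty is not a missing detail: outcome, treatment term and co-predictors are stated, and stated again for the power analysis. Second, tests of effects on the constructs are not tests of the total effect on activity. The article does not say outright which occasion's psychological scores enter each model. Scores from the same follow-up are the natural reading, since preceding values are handled in a separate sentence; a baseline-only reading has no support in the text.

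**Conclusion.** The concern holds in this form: the only specified model for the primary outcome yields, as its intervention coefficient, the effect left after mediation, while the hypothesis is the total difference between arms, and nothing names the total as the effectiveness result. The mismatch follows from the article's own account of the variables and needs no numerical assumption.

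Its size does. At an assumed total of 0.30 SD, reading the dummy coefficient as the result gives 0.15, 0.09 or 0.00 for mediated shares of 50%, 70% and 100%. The total effect, the shares, the 0.6 SD mediator shift and the confounder loading are not in the documents. The lagged adjustment adds to the understatement at one, three and six months, by an amount that cannot be computed from the article. The point deserves correction before analysis because it governs the main conclusion, but the documents do not show that the trial is bound to miss a real effect.

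**What to change.** 1. Name the total effect as the primary effectiveness result: out-of-school physical activity at each follow-up on condition, its pre-trial value and pre-trial covariates, allowing for school and class clustering. Enter no post-randomisation psychological variables and no post-randomisation lagged values.
2. Keep the model with the seven constructs as a secondary mediation analysis. State the paths from condition to the mediators, report direct, indirect and total effects, and acknowledge that direct and indirect effects assume no unmeasured confounding between mediator and outcome.
3. Confine adjustment for the preceding occasion to that secondary analysis, or replace it with the pre-trial value throughout.

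The cost is analysis wording and one simpler model; no new data are needed. The Sample size section would also need a sentence saying that 286 rests on model fit and not on a treatment difference. One related matter is not settled by this change: the wait-list teachers receive the autonomy-support training straight after the three-month follow-up (Procedure and data collection methods), so the report must say what the six-month contrast compares.
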